## Abstract

**Introduction:**

Today, accessing information on health issues is easier than ever. However, the flood of information can make decision-making difficult. Information can influence the intention for an action, yet the action often remains unpredictable. It is unclear if there is a relationship between the intention behavior gap and the wish for medical advice in parents of newborns as they have to deal with a number of vaccinations more than any other group of people. According to survey data, vaccine-hesitant people have less interest in vaccine advice.

**Methods and design:**

This study aimed to validate and elaborate this finding in a specific population and in a prospective observational manner. This study protocol was registered: https://drks.de/search/en/trial/DRKS00030716, DRKS00030716. The specific objectives include a primary endpoint focused on the wish for advice among hesitant and non-hesitant parents. Secondary endpoints involve comparing parents in terms of their respective information needs, which will be assessed based on: (a) vaccination attitudes at 6 weeks, (b) actual action taken at 12 weeks, and (c) the consistency of their attitudes and decisions. Parents of infants up to 6-week-old will be recruited and asked before the first recommended vaccination period and thereafter when the infant is 12 weeks old. Participants will receive an online questionnaire focusing on the information and advice they would like to receive and have received. Vaccination attitudes will be assessed using the C7C questionnaire at 6 weeks and the actual action of taking the first vaccine at 12 weeks.

**Discussion:**

INFORMed will provide data on information needs and wishes of young parents depending on their attitude toward vaccination. Based on the results, health literacy in parents can be improved and information strategies can be adapted.

## Introduction

It has never been easier to access information on any topic than it is today. Social media, in particular, offers many avenues for finding information, which can either undermine or reinforce one’s opinions. Evaluating the correctness of this information can be difficult, leading to uncertainty and confusion, especially in medical contexts. Patient preference is, next to expert clinical experience and current state of research, one of the three pillars of evidence-based medicine, but evidence for information strategies is very low and often focused on the view of healthcare experts. Many patients do wish to participate in the decision-making process (1, 2), yet information (3) and evidence show that especially hesitant patients tend to need individualized participatory formats (4). The decision process and way of education are based on different influencing factors and experiences.

Different strategies of participative decision-making have been developed over the years, which have in common that they can be time-consuming (5). Physicians are often working under time constraints, a factor that can contribute to limiting the extent to which they practice shared decision-making (6).

On the parents’ side, personal experiences influence their decision. As highly effective drugs, vaccines also have the potential to produce negative side effects that, although presumed to be rare (7), can be classified as threatening by parents (8). In this context, a lack of information seems to have a particular influence on decision-making to the effect that healthcare workers who provide more information are experienced, as being more trustworthy, resulting in a higher rate of vaccination (9). In some contexts, hesitant parents seem to wish less for information than non-hesitant parents (1). Good communication, which includes parents feeling understood (10), is then all the more important to answer open questions and to explain the current state of research (11). Even though there is research on shared decision-making and other forms of patient participation, it generally focuses on large population groups (1, 12) and seldom measures actual vaccine uptake (13, 14). Another difficulty with research in this area is that communication about vaccines cannot be compared between different vaccines as they cause different degrees of hesitancy (15).

The timing of the consultation could also play an important role, particularly in connection with childhood vaccinations. As immunization of infants is recommended as early as possible (16), one of the first decisions parents must take for their children after birth is whether they want to vaccinate as recommended or not, especially given that different countries have different recommendations. At no other time of life do humans face so many immunizations against as many pathogens as in the newborn phase and first year of life, on top of many other decisions, that this phase of family life requires. Hence, parents have to deal with much information at this time, and the vulnerable postpartum period can pose an extra strain on decision-making (16). Vaccinations are applied multiple times, but the most important is the first initial application, because parental experience of the first vaccinations may influence all following actions for their child (17). It is therefore particularly important to consider this phase of the first vaccination decision and make it as smooth as possible for the parents.

Considering these aspects, the study aims to ask new parents who they trust and what they need to make an informed and satisfying decision for their newborns. To improve research in vaccine promotion, parental attitudes must be investigated before and after the actual action of the initial vaccination consultation, which consists of two parts: the immunization advice and the initial vaccination itself. Hence, the immunization advice will be investigated in this study from the parental perspective. Furthermore, it is unclear what factors influence actions deviating from the parental vaccination attitude. Vaccine promotion has often the primary intention to persuade hesitant parents/patients and not the main aim to answer the expressed information needs of parents/patients. This implicit intention of each counseling session must be considered in analyses. This study is the first to distinguish these two intentions (persuasion and information satisfaction) in order to evaluate success in terms of the desire for counseling and actual vaccination. Therefore, parents will be asked before their first advisory and vaccination appointment about their needs and their attitude and after the first recommended time for vaccination about their experience, their action, and their suggestions for improvements. Since time management plays a major role in medical offices, one part of this study also deals with the search for information channels other than medical ones. The results may allow us to develop the underlying framework and promotion initiatives.

### Strengths of the study

- Exclusive focus on the population with the highest vaccination rate- Prospective and longitudinal- Differentiation between attitude and action- Differentiating between vaccination education in principle and information content- Information content checklist developed based on qualitative preliminary work (2)- Neutrally observing and not intervening, thus also reaching hesitant parents (4)- Theoretical framework examined in detail.

## Methods and analysis

This protocol is built in accordance with the STROBE guidelines (18) because it is a purely observational study.

### Study design

In contrast to most cross-sectional surveys with various ages, this investigation is planned (a) very early after the birth of the child and (b) as a prospective longitudinal study before and after the first vaccination. This purely observational study will exclusively focus on the parental view and does not entail a specific intervention. It is intended to assess requirements and needs for information and optimal vaccination intervention.

To minimize the stress associated with becoming a parent and expectation bias in the parent–pediatrician interaction, the study is designed as an online case report form, so that parents can easily answer the questions independently. This study is parent-based because the parents’ view is crucial for their decision.

### Sample selection

Physicians, midwives, social workers, and other professionals working with parents and parents-to-be register on the study website. For external validation, multiplicators answer a case report form that includes information necessary for the shipping of flyers, the profession of the multiplicator, and an adapted version of the 7C questionnaire to assess their attitude to vaccines.

Multiplicators hand out flyers to possible study participants and draw attention to the study. Depending on the professions of the multiplicators, flyers can be handed out to families with newborns younger than 6 weeks, for example, at the appointment for the U3 (a routine preventive medical checkup in Germany at the age of 4 to 6 weeks) or to expectant parents, for example, during preventive pregnancy checkups. Further advertising can take the form of posters, newsletters, or websites of multiplicators. If this way of recruitment does not result in sufficient participants, the use of less validated methods such as the distribution of the study website via social media could be discussed.

### Inclusion and exclusion criteria

As expectant and new parents get informed electronically via the study website, register and consent electronically in a separate REDCap database (19, 20), and participate via email, study participation is only possible for parents who have access to a digital device and have an email address. To guarantee consistent conditions, all participants need an affiliation with the German healthcare system. Furthermore, sufficient knowledge of the German language is needed.

Infants that are older than 8 weeks or families with one child already participating in the study will be excluded.

### Data collection

The registration process and consent to participation for parents should end before the infant gets its first immunization, which is according to the immunization schedule as soon as the infant is 6 weeks old. Registration must take place before the child has passed the age of 8 weeks, as this is the recommended time frame of the six-fold vaccination, which is sometimes given together with the rotavirus vaccine, which is recommended from 6 weeks on.

After registration, parents receive emails with further information depending on the age of the infant. Parents of unborn babies indicate the expected date of birth. They receive an email asking them to state the actual date of birth 3 weeks after this date. Parents of babies already born get invited to answer the first questionnaire as soon as their baby is 6 weeks old. The electronic case report forms will be stored in the Research Electronic Data Capture (REDCap) system (19, 20). Before the first question, parents get informed about the use and security of their data and their option to withdraw their consent to the use of their data. The first questionnaire in which parents get asked for their personal data, such as names and addresses, is kept in a database that is separate from the child’s health questions. A link between both databases is only possible via record linkage, with the email address being essential for sending invitation emails.

Parents will be interviewed via online case report forms at two time points. The first is before the first recommended vaccination, as mentioned before. The second time point occurs when the infant is 12 weeks old, as this is the time when the recommended time slot for the first immunization is over (Table 1). By this time, parents will have made decisions regarding whether and how to immunize their infant. If parents do not answer a questionnaire, they receive up to five reminder emails, which are sent every 5 days.

**Table 1 tab1:** Invitation and visit schedule of INFORMed study.

Separate visits	(V-1)	(V0)	V1	V2
Age of observed child (months)	Unborn*	<1 ½*	1 ½*	3
Informed consent	X	X	X	
True date of birth		X		
Attitude toward vaccination (C7C), demographic data, health status of the parents and siblings, and their vaccination			X	
Type of information, source of vaccination information, influencing factors, and trustworthiness of information sources			X	X
Details about vaccination advice and vaccination status				X

*Registration possible.

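### For parents who register before birth, the only described birth-date request goes out 3 weeks after the expected date, so V1 cannot be sent on time when the child is born more than 3 weeks early

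*Protocol article*

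**What the plan says.** All of this is in the protocol article; no fuller protocol or analysis plan is at hand.

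- **Entry before birth.** Under Data collection: "Parents of unborn babies indicate the expected date of birth". Table 1 gives these families a visit V-1, and Sample selection describes handing flyers to expectant parents.
- **Learning the true date.** The next step for them is: "They receive an email asking them to state the actual date of birth 3 weeks after this date". No earlier notification of birth and no rule for early births is described. Table 1 puts the item "True date of birth" at V0, with the child younger than 1 ½ months.
- **Timing of V1.** "Parents of babies already born get invited to answer the first questionnaire as soon as their baby is 6 weeks old". On its place relative to vaccination: "The first is before the first recommended vaccination, as mentioned before". The first immunization is due, in the article's words, "which is according to the immunization schedule as soon as the infant is 6 weeks old".
- **The 8-week limit.** Data collection ties it to registration: "Registration must take place before the child has passed the age of 8 weeks". Inclusion and exclusion criteria gives it without a reference time: "Infants that are older than 8 weeks or families with one child already participating in the study will be excluded".
- **What V1 carries.** The C7C attitude scale, which defines the hesitant and non-hesitant groups, is collected at V1 only. The primary endpoint is the wish for advice before the first recommended vaccination period, and the section on bias and limitations confirms that the primary analysis uses answers from the first questionnaire.

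**The concern.** The V1 invitation is triggered by the child's age, so for families who registered in pregnancy it cannot be timed until the study knows the birth date. The only described request for that date is anchored to the expected date, not to the birth. The earlier the child, the older it is when the study first asks.

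There is no slack at the other end. V1 is due at 6 weeks, the same age at which the first immunization becomes due. Any delay past 6 weeks moves both halves of the confirmatory comparison (attitude group and wish for advice) into the period they are meant to precede. It also affects the attitude half of the four attitude-by-action groups. The families concerned enrolled earliest and could most easily have given an answer before vaccination.

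**Working it through.** The protocol states no figure on this point to reproduce; the check is date arithmetic on its own rules.

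**Inputs from Data collection:** request sent at expected date + 21 days; V1 due at 42 days of age; registration limit 56 days of age; up to five reminders at 5-day intervals, stated for questionnaires. The sentence on the request could be parsed in more than one way, but an email sent 3 weeks after the expected date is the only reading that makes sense.

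**Step 1: age when the request is sent.** Age = 3 weeks + weeks born early (d).

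| Weeks early (d) | Age at request | Against V1 at 6 weeks |
|---|---|---|
| 0 | 3 weeks | 3 weeks in hand |
| 2 | 5 weeks | 1 week in hand |
| 3 | 6 weeks | due that day |
| 4 | 7 weeks | 1 week late |
| 5 | 8 weeks | 2 weeks late |
| 6 | 9 weeks | 3 weeks late |

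These ages assume a reply on the same day.

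**Step 2: the V0 slot in Table 1.** The table labels the 6-week visit 1 ½ months, so V0 (under 1 ½ months) means under 6 weeks and cannot be met from d = 3. Read as calendar months, 1.5 × 30.4375 / 7 = 6.52 weeks, and the slot is missed once d exceeds 3.52 weeks. The V1 result in step 1 does not depend on this choice.

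**Step 3: slow replies.** With a reply delay of L days, the child is at least 42 days old at reply when days early ≥ 42 − 21 − L = 21 − L.

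- L = 0: 21 days early
- L = 10: 11 days early
- L = 20: 1 day early
- L = 25: a child born on the expected date is 21 + 25 = 46 days old, or 6.6 weeks

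The last line matches five reminders at 5-day intervals. Applying the reminder rule to the birth-date email is an assumption.

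**Step 4: possible reach (assumptions, not in the article).** Suppose 25% to 100% of the planned 400 parents register before birth and 3% to 10% of births are at least 3 weeks early.

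- Low end: 400 × 0.25 × 0.03 = 3 families
- High end: 400 × 1.00 × 0.10 = 40 families

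This counts children who are 6 weeks or older when the request goes out. It includes those exactly 3 weeks early, whose V1 is still on time if the parents reply that day.

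**Step 5: effect of asking earlier.** If the first request goes out on the expected date, age at request = d weeks, so 6 weeks is reached only at d = 6. With a 10-day reply delay, 42 − 10 = 32 days early are needed instead of 11.

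**The case against.** **The study already accepts V1 after 6 weeks.** Registration is open until 8 weeks, and Table 1 allows consent and registration at V1 itself. A child 4 or 5 weeks early is therefore surveyed no later than a permitted late registrant. This stands and limits the seriousness. It does not remove the point: a late registrant arrives late by the family's own timing, whereas these families enrolled in time and are delayed by the study's schedule.

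**The 8-week limit.** A reader might infer that children more than 5 weeks early (35 days, since 56 − 21 = 35) are excluded or lost because they are past 8 weeks when the study learns of the birth. The documents do not support that. Data collection ties the limit to registration, which these parents have completed, and nothing says that a registered family is removed. The exclusion criterion names no reference time, so the two statements need reconciling.

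**Bias.** A reader might also infer a biased primary comparison, because parents of early-born children could differ in hesitancy or wish for advice. The article has nothing on whether they differ or in which direction, and no rule that discards late V1 answers.

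**Condensed article.** A birth-report link may already exist in the REDCap set-up. That is possible, since the article mentions age-dependent emails without listing their content. But the +3-week request is a stated rule, and as stated it cannot meet the V0 and V1 timing.

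**Burden.** One request at +3 weeks spares families emails around the birth, in keeping with the design's aim of limiting stress, and leaves 3 weeks before V1 for a birth on the expected date. That is a fair reason to keep the number of emails low, but not to rely on this request alone.

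**Conclusion.** The point holds for timing. With the request as described, V1 cannot be sent at 6 weeks to a family registered before birth whose child is more than 3 weeks early, however promptly the parents reply. At exactly 3 weeks early there is no margin. Ordinary reply delays extend the problem to children less than 3 weeks early. The consequence is a late V1, which may follow the first advice or vaccination and so may not measure what the primary endpoint defines.

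The mechanism follows from the article's own dates and needs no outside figure. The size does: 3 to 40 families of 400 rests on assumed shares, and the group is probably a minority. No effect on the result of the primary test has been shown, and exclusion at 8 weeks is not established. This is a modest scheduling fault that touches the primary measurement and is worth correcting while recruitment continues.

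**What to change.** 1. Put a personal link for reporting the birth in the registration confirmation sent to parents who register before birth.
2. Send the first birth-date request at or before the expected date, with a not-yet-born option, and keep the +3-week request as a follow-up.
3. Release V1 at once when the entered date shows that the child is already 6 weeks or older.
4. State whether the 8-week limit in Inclusion and exclusion criteria refers to age at registration, as Data collection implies, or to age at some later step.

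The cost is a changed schedule for one automated email, one link and one answer option, plus one or two extra emails per family registered before birth. Some of these will arrive close to delivery, so they should be short. Births more than 6 weeks early would still be caught late by a request on the expected date alone; the link, or a request sent before that date, covers them.

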### Quality control

The electronic capture allows logical consistency tests and in case of incomplete or unclear responses recognized during statistical monitoring, direct clarification with parents is undertaken.

### Patient and public involvement

The questions of the case report forms are based on a qualitative study with young parents. However, the wishes of young parents are not only considered in protocol development, but are a fundamental focus of this investigation, because the information needs are evaluated not from physicians, but from parents’ perspective.

In addition, participating parents are invited to regular meetings during the study to report on their experience with the study and to offer suggestions.

### Measurements

The main question of this study is if vaccine-hesitant parents with negative attitudes wish less vaccine advice, as reported. To elaborate this further, we evaluate if and what kind of vaccination advice has been given to the parents and what was missing in their opinion. To analyze the type of vaccination advice, the case report form at the first visit includes questions about:

The attitude toward vaccination will be assessed at the first visit using the C7C Scale (21). At the same time, confounding factors such as demographic data, health status of the parents and siblings, their vaccination status, and experience with vaccination will be assessed.Type of information based on a qualitative study (2) (e.g., effect and side effects, incidence and severity of the disease being vaccinated against, and information on divergent strategies)Source of vaccine information (Internet, books, circle of friends, midwife, and non-medical practitioner)Previous concrete understanding of the vaccination advice and strategyInfluence of professionals and of the social environmentTrust in professionals, social environment, and possible counseling centers

The second case report form at the age of 12 weeks (visit 2) contains the same questions, except the attitude toward vaccination but supplemented by information on:

The professional who gave the advice (e.g., pediatrician, general doctor, and additional or other specialties)Details about vaccination advice (separate appointment/in the context of prevention examination/only at the vaccination procedure/information by a counseling interview/in writing; which brochures were delivered, duration of vaccination advice, fulfillment of the parental expectations, change of vaccination decision by the advice given and in what way, and influence of vaccination decision on further medical care)Other sources of information (e.g., Internet, books, circle of friends, midwife, and non-medical practitioner)The actual action: vaccination status at 12 weeks.

